## Abstract

**Background:**

Sleep disordered breathing is a chronic condition often requiring patient commitment to positive airway pressure (PAP) therapy. Understanding the lived experience of PAP therapy users is crucial for clinicians to support successful treatment and identify research priorities. There is a lack of evidence in this area, and published data predominantly explore the negative experiences of PAP. This study aims to explore the lived experiences of patients using PAP therapy.

**Methods and analysis:**

This study employs a phenomenological approach, appropriate for researching human experiences where there is little existing research. Heideggerian theory underpins the research, recognising that the researcher’s beliefs influence meaning, allowing for rich analysis of the lived experience.

Participants will be recruited from a randomised controlled trial investigating the medium-term clinical impact of customised interfaces for patients requiring PAP therapy. Purposive sampling will be used to seek representation from various demographics, with a maximum of 30 participants.

Data collection will be via 1:1 semistructured interviews. Data will be analysed using Braun and Clarke’s six-phase reflexive thematic analysis. Data will be analysed inductively through an interpretivism lens. Data will be managed with computer-assisted qualitative data analysis software.

**Ethics and dissemination:**

This protocol has been approved by the Hampshire B Research Ethics Committee (REC reference: 22/SC/0405). Results will be disseminated to healthcare professionals and patients through conferences, open-access journals, newsletters, the study webpage, infographics, animations, social media and healthcare awards. Tracy’s eight ‘big tent’ criteria for excellent qualitative research are comprehensive and encompassing, and this protocol has aimed to meet the criteria. The Consolidated Criteria for Reporting Qualitative Research has also been used. The findings of this study will contribute to a more holistic understanding of the lived experience of PAP therapy users, informing clinical practice and future research.

**Trial registration number:**

ISRCTN74082423.

STRENGTHS AND LIMITATIONS OF THIS STUDYUses a phenomenological approach, which is well-suited for exploring the lived experiences of individuals, providing deep insights into the human aspects of positive airway pressure therapy.The use of Heideggerian theory allows for a rich and nuanced analysis by acknowledging the influence of the researcher’s beliefs on the interpretation of data.Uses Braun and Clarke’s six-phase reflexive thematic analysis, a robust and systematic method for analysing qualitative data, ensuring thorough and reflective data interpretation.The quality of data is dependent on the participants’ willingness and ability to articulate their experiences, which can vary significantly and could affect the richness of the data.The influence of the researcher’s beliefs, while acknowledged, may still introduce subjective bias into the interpretation of the qualitative data.

## Introduction

 Sleep disordered breathing is a long-term condition often treated with positive airway pressure (PAP) therapy, which requires ongoing commitment from patients to benefit from treatment. Comprehending the lived experience of patients undergoing PAP therapy could help clinicians support patients in achieving treatment success. Additionally, understanding the lived experience could help identify future research priorities. Furthermore, engaging patients in such technologies is critical as technologies improve.

A comprehension of the lived experience of patients undergoing PAP therapy could facilitate clinicians to support patients in successful treatment use. The addition of PAP therapy is disruptive to not just the individuals’ lives but also those around them.^1^ Untreated obstructive sleep apnoea (OSA) impacts wider society,^2^ and this wider impact goes unrecognised in the design of patient pathways. Furthermore, as patient pathways evolve, aiming to become more efficient, engaging patients in and appreciating their acceptance of such pathways is critical. A systematic interpretive literature review^1^ reported a paucity of information about the experiences of continuous PAP (CPAP) users from their perspective. Of the 22 studies included, only seven were qualitative in nature. The studies included had global representation, although all bar one were conducted in the Western world. The included studies represented patients with moderate to severe OSA. The duration of the included studies ranged from one night to 6 months. Six of the included studies represented patients who had discontinued treatment. There was a narrow focus of the research on factors that facilitated or hindered CPAP use. Thematic analysis of the included studies identified three themes related to experiences using CPAP: ‘*users’ beliefs about CPAP influence users’ experiences of CPAP’, ‘experiencing CPAP is investigated and reported as synonymous with experiencing difficulty’,* and ‘*spouse and family influence users’ experience of CPAP’*. Ward *et al*^1^ observed evidence of bias in reporting, with the research instruments used limiting exploration of negative experiences of CPAP. Brown *et al*^3^ focused on establishing reasons for non-concordance with PAP therapy in their systematic review and thematic synthesis. They report four themes: ‘*journey to PAP’, ‘discomfort from and around PAP’, ‘adapting to and using PAP’* and ‘*benefits from PAP’*. Brown *et al*^3^ acknowledge there is little existing qualitative research investigating the lived experience of PAP therapy. They reflected on the applicability of a biopsychosocial understanding of PAP therapy and suggested ways in which services could address barriers to PAP therapy concordance. More recently, in their content analysis, Simon *et al*^4^ highlighted the importance of understanding the lived experience in order to develop adherence-promoting interventions. The research to date has focused on PAP therapy adherence, and by not accounting for the whole lived experience, our understanding becomes constrained. This limited understanding could mean that current clinical pathways are misaligned with the lived experience. Qualitative research, particularly phenomenology, facilitates the amplification of the patient voice. There is a need for further qualitative research that aims to fully encompass the entirety of the lived experience of PAP therapy users.

### Aims

To explore the lived experiences of patients using PAP therapy.

## Methods and analysis

### Study design and theoretical framework

This qualitative study is nested within a randomised controlled trial (RCT). A phenomenological approach has been chosen for this qualitative research study as it is appropriate for researching human experiences where there is little research into the phenomenon of interest and to allow an increased insight into lived experiences.

The research will use a phenomenological approach underpinned by a Heideggerian theory.^5^ Phenomenology with a Heideggerian perspective recognises that the researcher’s beliefs influence meaning. Given that the primary researcher ([name]) is an experienced clinician in sleep and ventilation medicine, it will be challenging to bracket beliefs; hence, a phenomenological approach with a Heideggerian perspective is most appropriate. A Heideggerian phenomenological approach allows for rich analysis and facilitates the understanding of multiple facets of the lived experience, providing a more comprehensive ontological (the experience of existence experienced by individuals) perspective of Being.^5^ As such, Heideggerian phenomenology recognises the importance of everyday context, thus enriching the analysis and providing a holistic view of the lived experience (Being), such as daily lives, relationships and societal and environmental aspects of living. Existential exploration is a core component of Heideggerian phenomenology, and this existential lens facilitates an analysis that goes beyond description and delves into the fundamentals of Being. Key aspects prioritised within Heideggerian phenomenology are depth, context and participant perspectives. These components empower the researcher to uncover the essence of the lived experience.

### Sampling/recruitment

#### Participants

Participants will be recruited from those participating in both arms of an RCT (3DPiPPIn). The RCT has been designed as a pragmatic trial and is embedded into existing clinical pathways. The 3DPiPPIn trial investigates the medium-term clinical impact of customised interfaces for patients requiring PAP therapy. Patients recruited will be under a specialist sleep and ventilation team in a secondary/tertiary care setting.

#### Sample

The study will recruit participants from the intervention and control arms of the 3DPiPPIn RCT to gain a range of experiences. The study aims to recruit a maximum of 30 participants.^6^ Purposive sampling will be used to seek broad representation from a variety of demographics (age, sex, ethnicity and concordance with PAP therapy), aiming for the sample to represent maximum variation by key selected characteristics for this study.^7^

#### Inclusion criteria

Patients participating in the 3DPiPPIn trial.Diagnosis of sleep-disordered breathing: Apnoea Hypopnoea Index (AHI)≥15.Patients naive to domiciliary PAP therapy.Age≥18 years.

#### Exclusion criteria

Patients unable to provide informed consent.AHI<15.Excessive facial hair, which they are unwilling to shave.Age <18 years.Existing facial pressure ulcers.Unable to provide informed consent.Known allergy to silicone.Keloid scarring.Previous domiciliary PAP therapy.

### Data Handling and Analysis

#### Data collection and development of the topic guide

Data collection will be via 1:1 semistructured interviews. Participants will be given a choice between face to face interviews at the Royal Free Hospital or online via a virtual videoconferencing platform. Through piloting and feedback from patient and public involvement and engagement (PPIE) groups, it is recognised that a choice between Zoom and Microsoft Teams increases acceptability and access to participation. Thus, both platforms will be offered to participants. Face to face interviews will be recorded using Samson Go Mic (Samson Technologies Corp, New York, USA). Interviews conducted via virtual videoconferencing platforms will be audiovisually recorded. Semistructured 1:1 interviews have been chosen to allow for depth and breadth of response while allowing flexibility for participants. In keeping with the Heideggerian phenomenological approach, the interviews will be indepth and dialogical in nature. The researcher aims to ensure the depth of participants’ responses. Thus, when they provide descriptions, the researcher will prompt exploration through probing and encourage the use of examples to illuminate the descriptions.^8^ It is recognised in Heideggerian phenomenology that the subjective judgement of the researcher is valuable. However, the researcher will aim to ensure the participant’s perspective is the focus of the research and avoid leading questions. Reflection and clarification will ensure that participants’ meaning is understood. Active listening techniques will be deployed throughout the interviews to convey interest and enhance rapport. Interviews will be transcribed verbatim using a general data protection regulation (GDPR)-compliant transcription service (Typeout, UK), with transcripts reviewed by the participants for accuracy.

#### Topic guide

An initial topic guide was developed based on the research aim, clinical experience and literature from the systematic review, which was reviewed by the trial PPIE group. The topic guide is designed to ensure participants feel comfortable, build rapport and assure depth of response regarding the lived experience. Opening questions are broad, questions are grouped around particular topics and more sensitive questions are asked later in the interview once rapport has been established. The topic guide and interview process were piloted with one member of the PAG who was a current PAP therapy user. The pilot interview was transcribed verbatim using a transcription service (Typeout, UK). The pilot interview recording and transcription were reviewed by an experienced qualitative researcher (CK) who provided feedback and guidance on how the interview was conducted to ensure it was in keeping with the philosophical framework described above. The participant reviewed the transcripts for accuracy. Amendments to the topic guide were made accordingly, with the order of some questions adjusted. The topic guide is designed as an aide-mémoire for the researcher to ensure the depth and breadth required of a phenomenological approach. The topic guide is not intended to be limiting and aims to enhance rapport. Additional questions will be asked where needed to ensure that the data collected represents the participant’s lived experience. The topic guide includes prompts regarding expectations, health, societal impacts, work, leisure, lifestyle and sources of advice.

#### Data storage and confidentiality

Data storage aligns with the UK Data Protection Act 2018, which sets out the GDPR. University College London (UCL) accounts for both Zoom and Microsoft Teams will be used for the videoconferencing interviews. This ensures that data are both collected and stored securely. Participants will provide informed consent via an electronic consent form. Transcripts will be anonymised after participants have reviewed them for accuracy. Interview recordings will be kept until the transcription is complete and will subsequently be destroyed in line with the UK Data Protection Act 2018.

#### Data analysis

Multiple analytical approaches are possible when undertaking a phenomenological-based study. Braun and Clarke’s reflexive thematic analysis^9^ is a flexible and helpful method for analysis and can be used within several theoretical frameworks, including phenomenology.^10^ Reflexive thematic analysis is often considered to be more accessible than other analysis methods. Reflexive thematic analysis provides a rich and detailed account of data, allowing for deep exploration of the lived experience and is thus compatible with a Heideggerian phenomenological approach. Braun and Clarke’s reflexive thematic analysis supports both an inductive and deductive approach to data analysis. Inductive analysis is strongly linked with the data and allows the researcher to immerse themselves in it. Data will be analysed inductively with an interpretivism lens, which assumes the world is interpreted through our experiences and accounts for the impact cultural and societal concepts have on the context of our experiences.^10^

Data will be analysed using Braun and Clarke’s phase reflexive thematic analysis approach.^9^

Familiarisation phase: this involves reading and rereading the data to become immersed in and intimately familiar with its content.Coding phase: this involves generating succinct labels (codes) that identify important features of the data that might be relevant to answering the research question.Generating initial themes: this phase involves examining the codes and collated data to identify significant broader patterns of meaning (potential themes). Then data are collated relevant to each candidate theme.Reviewing themes: candidate themes are checked against the dataset to determine that they tell a convincing story of the data and answer the research question.Defining and naming themes: for each theme, this phase involves developing a detailed analysis, working out the scope and focus and determining the concept.Writing up: this final phase involves weaving together the analytic narrative and data extracts and contextualising the analysis in relation to the existing literature.

Triangulation will be sought from the data within the RCT for concordance between data sets to deepen insights and understandings. Data will be managed with computer-assisted qualitative data analysis software (NVivo V.14 plus).

#### Secondary analysis

A secondary analysis using a large language model will enhance the qualitative analysis. A large language model is a type of artificial intelligence trained using vast amounts of text. These models can generate human-like responses and help simplify complex information. Large language models do not directly access personal information; they learn patterns from combined data. The use of large language models for qualitative data is rapidly expanding in marketing, but few healthcare academics have yet to use this tool. The benefits of using a large language model for qualitative analysis include reduced time and potentially reduced bias. Transcripts will be uploaded into a large language model. Prompts will be developed by a member of the research team ([name]) to provide context to the large language model. The prompts will follow a model of constraining the model using a thematic analysis with a phenomenological underpinning. Context regarding the researcher will also be used as a prompt. The prompts will follow a ‘you are’, ‘I am’ and ‘I want you to’ approach. Prompts will be peer-reviewed by a researcher with experience using large language models for qualitative analysis. Transcripts will be anonymised prior to being entered into the large language model.

The value, efficacy and practicality of using large language models to support qualitative analysis will be considered. These factors will include:

Percentage of patients providing consent for their data to be used in the secondary analysis.A comparison of theme outputs between traditional models and using large language models.Data validation.Time efficiency: time taken to analyse themes with and without large language models.Consideration of bias and whether this is reduced or increased by the addition of the large language model being employed in the analysis.

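### The theme comparison used to judge the language model cannot tell a theme drawn from these transcripts from a generic one; a single run without transcripts would help

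*Protocol article*

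**What the plan says.** The relevant text is mostly in the Secondary analysis section of the protocol article.

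- **What the model is.** "A large language model is a type of artificial intelligence trained using vast amounts of text"; the section adds that "they learn patterns from combined data". No model is named.
- **What it is given.** "Transcripts will be uploaded into a large language model", after anonymisation. On the prompts: "The prompts will follow a model of constraining the model using a thematic analysis with a phenomenological underpinning". Also: "Context regarding the researcher will also be used as a prompt". A researcher experienced in this use of language models peer-reviews the prompts.
- **How it is judged.** One listed factor is "A comparison of theme outputs between traditional models and using large language models". The same list includes data validation, with no further description, and a consideration of whether the model lowers or raises bias, with no method given.

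For the main analysis, the Data analysis section states: "Data will be analysed inductively with an interpretivism lens". Its fourth phase has the human analyst check candidate themes against the dataset.

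**The concern.** The question behind the secondary analysis is whether a language model can usefully analyse these interviews. That requires evidence that its themes come from the interviews. A model trained on general text may be able to produce plausible themes about living with PAP from what it has already absorbed. If such a theme coincides with a human one, comparing theme outputs shows a match but not how the model reached it.

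At stake is the conclusion on the model's value and efficacy, which could credit it with more extraction from the data than it performed. There is also a link to the study's rationale. The Introduction criticises earlier work for concentrating on adherence and on difficulty with treatment. A model that falls back on published framing could bring that emphasis back under the appearance of a finding from these participants.

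**Working it through.** The article gives no agreement statistic, threshold or matching rule, so there is no figure to reproduce. The check is a reading of the text.

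1. **Prior content.** The article says the model is trained on general text. It does not say that this text covers PAP. The Introduction shows that PAP themes are in print: three from one review and four from another. That an unnamed general model has met such material is a reasonable assumption, not a stated fact.

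2. **Constraint on source.** The stated prompt constraint covers analytic method and philosophical underpinning. Context about the researcher is a further input that is not transcript. Nothing described restricts the output to the uploaded text. Peer review of prompts examines what goes in, not whether the themes that come out are grounded.

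3. **Grounding check on each side.** Human candidate themes are checked against the dataset. No equivalent step is stated for model themes.

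4. **What the comparison can show.** The possible cases are:

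| Source of the model theme | Human analysis has the same theme | Human analysis does not |
|---|---|---|
| Drawn from the transcripts | match | difference |
| Generic, returned without using them | match | difference |

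The two rows give the same result in each column, so theme outputs alone do not identify the source. In the match column the model may be credited with extraction it did not perform. In the difference column a generic theme counts as a discrepancy, which does not flatter the model.

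5. **Size.** This would need the share of matched themes that the model would also return without transcripts. The article gives neither that share nor a number of themes, so any percentage would be invented.

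**The case against.** The strongest reply is that this is an article condensing a fuller protocol. Data validation and consideration of bias are both named as evaluation factors, either could cover the point, and their detail may sit elsewhere. That stands as far as it goes: the lack of detail under those two items is not itself a fault. What remains is that the one comparison the article does describe cannot separate the two sources.

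A second reply also has force. A model theme that matches a human theme matches something the human analyst checked against the data, so the theme is probably present in the interviews. Only how the model reached it is in doubt. That is still the question when the model's value is being judged.

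Several stronger readings are tempting, and the document does not support them:

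- *The model holds PAP literature, or the prompts name PAP.* Neither is stated.
- *The plan would count recalled themes as agreement.* No agreement rule or scoring is given; the supportable statement is that the comparison could not distinguish them.
- *The comparison as a whole is biased toward agreement.* Invented themes with no human counterpart would appear as differences, so an overall direction is not established.
- *The topic guide gives both analyses a shared published source.* The Topic guide section does say "An initial topic guide was developed based on the research aim, clinical experience and literature from the systematic review", but the guide shapes the interviews and so acts through the transcripts that both analyses read. The section also says the guide is not meant to limit the interview.
- *Verified quotations would settle the matter.* A model can attach genuine extracts to a theme it already held.

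**Conclusion.** The point holds in a limited form. As described, the comparison of theme outputs cannot separate a theme the model drew from these transcripts from a generic theme that the human analysis also reached, so it could overstate what the model extracted. This rests on two assumptions: that the training text includes PAP material, and that the unspecified data validation and bias items do not already include such a check. The size is not estimable from the document.

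A reader might infer that the study's findings on lived experience are compromised. They are not: the aim is served by the human reflexive analysis, which has its own check against the data, and the language model analysis is secondary and separately consented. This is a low-cost improvement to a secondary question, not a flaw in the main design.

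**What to change.** Add three steps to the secondary analysis:

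1. **Before upload**, run the same peer-reviewed prompts once, on the same model, without transcripts, and file the themes returned. Record whether the prompts name PAP: if they do not, an empty result says little about prior content that the transcripts themselves might call up.
2. **For each model theme**, require verbatim extracts and confirm them by text search in the anonymised transcripts. Describe this as a screen for invented content, not as proof of origin. It would also give the data validation item a definite meaning.
3. **In the comparison**, report separately the themes that fail the extract check and those already returned without transcripts. Do not exclude the latter, since they may also be present in the interviews.

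The cost is one extra model run and some text searching, a few hours in all, plus analysis-plan wording. No new participant data are needed. The downside is that the model may look less favourable.
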